### Participants

Due to the longitudinal nature of the study which necessitates two data collection points, the focus of this study is on students in the 8th and 9th years of formal schooling. Based on a previous study that used a similar design to test the efficacy of ICC-T in Tanzania [30], we would expect a moderate to large effect on students’ self-reported exposure to violence. An a priori power analysis (α = .05, power = 0.80, moderate effect size of ƒ = 0.25) using G*Power software [40] indicated a required total sample size of at least *n* = 128 students to detect significant interaction effects. To adjust for the nested design of the study, we calculated the following design effect (DE): DE = 1 + (fixed cluster size considering drop-outs − 1) × intra-cluster correlation coefficient. Considering 60 students per school, a drop-out rate of 20%, and an intra-cluster correlation coefficient of 0.05, the DE for the student sample is 3.35, which results in a required sample size of at least 430 students. We aim to randomly select, at each school, 30 students from Senior One (8th year) and 30 from Senior Two (9th year). The target sample will thus be 720 students in the age range between 12 and 17 years. At the classroom level a list of all students will be obtained from the school administration. Stratified random sampling will be used to select 15 boys and 15 girls from each class or stream.

All teachers who are officially working in the selected schools will be included in the study sample. Based on the previous study in Tanzania [30], we would expect a large effect on teachers’ self-reported use of violence against students. An a priori power analysis (α = .05, power = 0.80, moderate to large effect size of ƒ = 0.35) using G*Power software [40] indicated a required total sample size of at least *n* = 67 teachers to detect significant interaction effects. To adjust for the nested design of the study, we again calculated the DE. Considering a minimum of 15 teachers per school, a drop-out rate of 20%, and an intra-cluster correlation coefficient of 0.05, the DE for the teacher sample is 1.55, which results in a required sample size of at least 104 teachers. Our target sample will be at least 15 teachers per school, resulting in a total sample of at least 180 teachers.

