### Analysis

Primary analysis will be carried out based upon the groups as randomized (“intention to treat”). We will use the last-observation-carried-forward approach; i.e., in drop-outs we assume no change from pre-assessment to follow-up. Results will be presented including appropriate effects sizes and a measure of precision (95% confidence intervals).

Our main analysis of the primary outcomes, students’ exposure to and teachers’ use of physical and emotional violence, will be *time × group* interaction effects using repeated multivariate analysis of variance (MANOVA). In case of a noted cluster effect (intra-cluster correlation coefficient > .10) we shall use multilevel analysis. Multivariate interaction effects and the univariate interaction effect of each outcome variable will be tested first. Paired *t* test analysis will examine the differences from the pre-assessment to follow-up assessment in the intervention group while the independent *t* test will examine whether there is a difference between the control group and intervention group at the follow-up assessment. Effect sizes η^2^ ≥ 0.01, η^2^ ≥ .0.06, and η^2^ ≥ 0.14 will be considered to represent small, moderate, and large effect sizes correspondingly. For *t* tests effect size interpretation will be guided by the suggestion of Cohen where *d* ≥ 0.20, *d* ≥ 0.50, and *d* ≥ 0.80 will represent small, medium, and large effect sizes, respectively.

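### The main analysis allows for school only if the observed ICC exceeds .10, although schools are randomised and the trial is sized for an ICC of 0.05

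*Protocol article*

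**What the plan says.** The Study design and Discussion sections of the protocol article describe a two-arm cluster trial with six schools per arm. The Analysis section makes the time-by-group interaction from a repeated MANOVA the main test for students' exposure to violence and teachers' use of it. It then adds: "In case of a noted cluster effect (intra-cluster correlation coefficient > .10) we shall use multilevel analysis". An independent t test between arms at follow-up is also planned, with no cluster adjustment stated.

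The Participants section treats clustering differently. It starts from "An a priori power analysis (α = .05, power = 0.80, moderate effect size of ƒ = 0.25", which "indicated a required total sample size of at least *n* = 128 students to detect significant interaction effects". It then applies a design effect: "Considering 60 students per school, a drop-out rate of 20%, and an intra-cluster correlation coefficient of 0.05" leads to "the DE for the student sample is 3.35, which results in a required sample size of at least 430 students". For teachers the effect size is "moderate to large effect size of ƒ = 0.35" and "the DE for the teacher sample is 1.55".

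Two other statements bear on the size of the problem. The Analysis section carries the last observation forward for drop-outs, which keeps them in the analysis. The Schools section takes two schools per district so that they can be randomly assigned to the two conditions. This suggests assignment within district pairs, although the Study design section does not say so.

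**The concern.** The design effect enters the sample size and is then left out of the analysis. At an ICC of 0.05 the trigger is normally not reached, so students and teachers would be analysed as independent although whole schools were allocated. P values and 95% confidence intervals for the primary outcomes would then be too optimistic.

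The trigger is also set on the wrong quantity. Variance inflation depends on 1 + (m − 1) × ICC, not on the ICC alone. With 48 students per school, an ICC just under .10 carries a design effect of about 1 + 47 × 0.10 = 5.7 and would still be ignored. Twelve schools also estimate an ICC too imprecisely for the estimate to choose the model.

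**Working it through.** **Inputs** (Participants, Study design, Analysis and Discussion sections): 12 schools, 6 v 6; 60 students and at least 15 teachers per school; 20% drop-out, leaving 48 and 12; planning ICC 0.05; f = 0.25 (d = 0.5) for students and f = 0.35 (d = 0.7) for teachers; alpha 0.05; switch at an ICC of .10.

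**1. The plan's own figures.** Noncentral F power with one numerator df gives N = 128 and N = 67, as stated. The design effects are 1 + 47 × 0.05 = 3.35 and 1 + 11 × 0.05 = 1.55, as stated. Then 128 × 3.35 = 428.8 (stated 430, a rounding difference) and 67 × 1.55 = 103.85 (stated 104). The sample-size step is sound.

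**2. Error of the unadjusted test.** Type I error ≈ 2 × (1 − Φ(1.96/√DE)).
- Students, 48 per school: √3.35 = 1.83, so 28.4%. Intervals are too narrow by that factor of 1.83.
- Students, 60 per school (all drop-outs kept): DE = 1 + 59 × 0.05 = 3.95, so 32.4%.
- Teachers, 12 per school: DE = 1.55, so 11.5%.
- Teachers, 15 per school: DE = 1 + 14 × 0.05 = 1.70, so 13.3%.

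**3. Error of the rule as written.** Null trials were simulated with 6 v 6 schools and no district effect. A univariate individual-level test is used if the estimated ICC is at most .10; otherwise a school-level t test on 10 df stands in for the multilevel analysis.

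| Outcome, number per school | True ICC | Rule switches | Error under rule | Always school-level |
|---|---|---|---|---|
| Students, 48 | 0.01 | about 0% | 10.5% | 4.9% |
| Students, 48 | 0.02 | about 0% | 15.8% | 4.8% |
| Students, 48 | 0.05 | 6% | 27.1% | 5.4% |
| Students, 48 | 0.10 | 44% | 23.7% | 5.0% |
| Students, 60 | 0.05 | 5% | 31.2% | 4.7% |
| Teachers, 12 | 0.05 | 17% | 9.8% | 5.1% |
| Teachers, 15 | 0.05 | 15% | 11.5% | 5.1% |

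Even at a true ICC of 0.10 the unadjusted test is used in 56% of trials.

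**4. If schools are assigned within district pairs.** The share of between-school variance lying between districts is an assumption. For students with 48 per school at ICC 0.05, error under the rule is 22.6% at a share of 25%, 17.6% at 50% and 10.9% at 75%. For teachers with 12 per school it falls from about 8.5% at 25% to about 5% at 75%. An unpaired school-level test is then conservative: 3.4%, 1.8% and 1.0% for students at the three shares.

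**5. If 0.05 is a cross-sectional ICC.** The ICC of change is ρ(1 − r_s) / [ρ(1 − r_s) + (1 − ρ)(1 − r_i)], where r_s and r_i are the school-level and individual-level correlations over time. The article gives neither. With ρ = 0.05, r_s from 0 to 0.9 and r_i from 0 to 0.7 (assumed), it runs from 0.005 to 0.149. The unadjusted student error at 48 per school then runs from about 8% to 49%. Where the resulting ICC is above .10, the rule would usually switch.

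**6. Power once school is always modelled.** For students at d = 0.5 and ICC 0.05, SE = √(2 × 3.35 / (6 × 48)) = 0.1525 and d/SE = 3.28. Power is about 0.84 on 10 df and about 0.75 on 5 df. For teachers at d = 0.7 with 12 per school it is about 0.86 on 10 df.

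**The case against.** The strongest objection concerns the size of the error. A reader might infer that the plan inflates type I error to 27% throughout. The document does not support that as a single figure, for four reasons.
- It applies to student outcomes only. Teachers' use of violence is equally primary, and there the figure is about 10% to 11.5%.
- It takes 0.05 as the ICC of change. Stable differences between schools cancel in a time-by-group test, and the article does not say which ICC it means. Still, the Participants section applies the design effect directly to the interaction test.
- It assumes no district effect. Paired assignment lowers the figure, for teachers almost to nominal.
- It comes from a univariate test. The multivariate interaction test was not simulated.

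A reader might also count 576 students (12 × 48) as the analysed sample. Carrying observations forward keeps up to 720, which makes the error larger, not smaller.

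Nor does it follow that a positive result could never be separated from ordinary school differences. School-level data would still permit a valid analysis; the fault lies in the analysis that is planned.

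These points change the size and not the defect. An unseen analysis plan or fuller protocol does not excuse it either, because the article states the rule and its threshold outright and provides no other cluster adjustment.

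**Conclusion.** Wrong as written. The analysis rule conflicts with the plan's own sample-size assumption, and under that assumption the primary analysis ignores the unit of randomisation.

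For students the error stays above nominal in every scenario computed, including about 11% at an ICC as low as 0.01. The 27% and 31% figures hold only if 0.05 is the ICC of the tested change and districts carry no variance. For teachers the inflation is smaller, and it nearly disappears if assignment is paired and most of the between-school variance lies between districts. The exact size is therefore not established, but the need to remove the rule does not depend on it.

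**What to change.** Delete the ICC condition, and with it the unadjusted MANOVA and t-test comparisons between arms. In the student and teacher primary analyses, always account for school, either by a mixed model with a school random effect and a small-sample df correction or by a school-level analysis. State whether assignment was within district pairs. If it was, include district (about 5 df); if not, about 10 df are available. Report the estimated ICC as a result and not as a gate.

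The cost is one paragraph and wider intervals, with no extra schools or data. The sample size was already inflated for clustering, and power at the planning ICC stays as shown in step 6. If the ICC of change were 0.10, power would be lower. With 576 students the plan's own formula leaves 576/5.7 = 101 effective students and power of about 0.70. A school-level test on 10 df gives about 0.62. These are two different methods and should be reported separately.

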### Ethical considerations

Given that the research involves human subjects considered as a vulnerable group, i.e., children [44], ethical clearance was obtained from the relevant ethical boards. The Mbarara University of Science and Technology Research Ethics Committee (MUST15/10-15), the Uganda National Council of Science and Technology (SS 4032), and the University of Konstanz Ethic Review Board (35/2016) have already approved the study.

Only pre-assigned codes will appear on the questionnaires and consent documents. Data will be stored on a password secured computer accessible to only the study investigators. Data obtained during the research will be kept confidential and will not be disclosed to another person without the participant’s permission or as required by the law. Behavioral intervention studies are minimum risk studies. However, in case of any unexpected adverse effect the researchers will document and report such occurrences to the respective ethical bodies within 1 week. Questions about experiences may evoke upsetting memories in the event that the participant experienced similar events in his or her life. Participants who will experience any psychological distress during the course of the data collection will be provided with psychological support by the research team members. For participants who experience adverse or unexpected events, appropriate referrals and follow-up for specialized services and further management will be made on a case-by-case basis.

## Discussion

Research findings, media reports, and non-governmental organization reports have provided anecdotal evidence about the prevalence, magnitude, and consequences of violence against children in Uganda [8, 13, 17–19, 45]. However, violence in school settings is still prevalent in Uganda despite efforts to protect children from violence through legal means. While Uganda has policies that ban violence by teachers at school [15, 16], these legal measures need to be followed up with practical ways of handling disciplinary issues in the education locale. Despite the increase of violence against children, few school-based interventions which aim at reducing violence by teachers have been evaluated for their effectiveness [3]. In Uganda, no violence prevention interventions have been scientifically evaluated at the secondary school level to the best of our knowledge.

Our study aim is to implement and evaluate the ICC-T intervention, which aims to reduce violence by teachers at school. The study will adopt a two-arm cluster randomized controlled trial design, with six schools allocated to the intervention group and six control group schools. The study will use a large sample that is representative for the government-aided secondary schools in the southwestern region of Uganda. The experimental design will allow referring of potential interaction effects to the intervention, and it controls for most potential confounds. Additionally, our results may be generalizable to similar school settings in Uganda and the region.

The study takes on a multi-informant approach, as data will be collected from a sample of teachers and students. We shall elicit self-reports from students and teachers in relation to school violence. Hence, the teachers’ self-reports will, in part, be complemented by the viewpoints of students. Furthermore, the instruments adopted for the study have a good theoretical basis and have proven to be reliable in measuring students’ exposure to and teachers’ use of school violence and in screening for mental health problems in East Africa [1, 21, 30, 32, 37, 38, 42].

The proposed study results may have implications for schools, teacher training, and policy in Uganda. Teachers’ continued use of violence despite policies that ban its use points to problems with teacher training in Uganda. Intervention approaches, such as ICC-T, that reduce violent disciplinary measures need to be implemented and evaluated at the school level. This may result in the frequent use of non-violent disciplinary methods in schools. Furthermore, regular teacher training needs to be enriched with respect to management of students’ behavior, alternatives to corporal punishment, and fostering of better teacher-student relations. Thus, the results of our study may help the Ministry of Education, Science, Technology and Sports to implement the relevant guidelines and programs that prohibit school violence in a more practical way. Moreover, there is a need to inform education sector stakeholders about the laws that ban the application of violent disciplinary measures in schools, children’s rights, teacher code of conduct, domestic violence laws, and the consequences of violating the applicable laws. Reporting procedures, monitoring guidelines, and review mechanisms must be enshrined in the broader legal implementation plan [8, 15, 16]. Research findings — to which our proposed study may also contribute — are vital in helping the population at large understand the negative effects of school violence.

The proposed study has some limitations. Self-report questionnaires are prone to possible respondent bias and social desirability. Furthermore, the proposed 3-month period between the intervention and follow-up assessment is rather short. The anticipated changes in attitudes and behavior can be regarded as preliminary in nature. Further, the inclusion of relatively few schools limits the generalizability of the study findings. One anticipated problem is the fluctuations in the number of respondents. Teacher attrition can be associated with retirement, routine transfers of civil servants, and resignation, among other causes, while students can drop out of school or transfer to other schools not in the study area. Additionally, there are strong sociocultural factors, attitudes, and beliefs that support the use of violence against children. Nevertheless, involving the teachers in creating the change and formulating their own training may help to promote engagement in the process. Reflections about the teachers’ own experiences of harsh punishment and violent discipline, discussions about consequences of violence for children, and the intensive practice of effective non-violent discipline strategies may facilitate a change of attitude regarding violent discipline. We thus believe that the intervention may enable teachers to visualize the link between violence and the associated negative consequences. This may persuade teachers to embrace alternative disciplinary approaches in schools.

ICC-T is an interactive intervention in which teachers can learn how non-violent discipline measures can be implemented in a real-life school setting in a practical way. It is easily applicable to the school settings in low-income countries and can be scaled up to other government-aided schools in Uganda. Making the school environment a safe place that is free from violence has great potential to contribute to the attainment of Goal Number 16.2 of the United Nations Sustainable Development Goals 2015–2030, which aspires to end all forms of violence against children.

### Trial status

The trial preparation phase is ongoing until July 2018. Intervention pilot test took place in May 2018. Pre-assessment (control and intervention schools) is scheduled from July–November 2018. Interventions are planned from August until December 2018. The follow-up phase will start in December 2018 and end by April 2019.

## Abbreviations

CTS: Conflict Tactics Scale
DE: Design effect
ICC: Interaction Competencies with Children
ICC-C: Interaction Competencies with Children for Caregivers
ICC-T: Interaction Competencies with Children for Teachers
MANOVA: Multivariate analysis of variance
SDQ: Strengths and Difficulties Questionnaire
USE: Universal Secondary Education
